## Abstract

**Background:**

Living with a smoker is a key determinant of exposure to Second Hand Smoke (SHS) and its exposure mainly occurs at home. Exposure to SHS from tobacco in the household predisposes to the development of tuberculosis (TB) and outcome of the disease gets worse. We aim to develop and evaluate a behavioural intervention 'Smoke Free Homes’ (SFH) for TB patients that encourages them to negotiate a smoke free environment within their homes.

**Methods and design:**

The pilot individual randomised controlled trial of SFH will inform the design of a future definitive trial. We will first develop SFH intervention using taxonomy of behaviour change techniques aimed at encouraging families of non-smoking TB patients to implement smoking restrictions at home following a logic model of the intervention. This will be followed by conducting a pilot randomised controlled trial of intervention within the context of routine TB control programme. The eligible non-smoking TB patients will be randomised and allocated to one of the two trial arms consisting of “individual based care” and “individual based care” plus “supplementary support”. We aim to recruit 150 newly registered pulmonary TB patients from two selected TB centres with 75 cases in each arm. The *Primary outcome* measure will be SFH of non-smoker TB patient by validating through 'Urine Cotinine’ test. We will also determine qualitatively the barriers and key drivers to the creation of smoke free homes followed by developing a definitive trial.

**Discussion:**

The male to female distribution of TB cases in Pakistan is almost equal whereas, tobacco use among males is much high as compared to females in Pakistan. This reflects a strong possibility that women health can be affected by men behaviour. Appropriate storage, restricted access and disposal arrangements for participant’s personal details will be implemented. All ethical issues will be addressed. There will be no extra burden, financial or otherwise, on the participants. They will not receive any financial incentive to participate in the study.

**Trial registration:**

Trial Registration Number: ISRCTN83630841

## Background

### Second hand smoke

Second-hand smoke (SHS) is a combination of 'side stream’ smoke from the burning tip of a cigarette and 'mainstream’ smoke exhaled by the smoker (Fielding and Phenow 1988). Toxic chemicals from SHS cling to rugs, curtains, clothes, food, furniture and other materials. These toxins remain in the environment despite open windows, fans or air filters; and can recycle back into the air through the filters and coat the surfaces of rooms, materials and smoker's belongings (World Health Organization 2009). Second-hand smoke kills 600000 people each year and its exposure contributes to an increased risk of cardiovascular diseases, lung cancer, asthma and other respiratory diseases both in adults and in children (World Health Organization 2009; Reddy and Gupta 2004). Living with a smoker is a key determinant of exposure to SHS and it occurs mainly in homes. The General Adult Tobacco Survey in India shows that 52% of the adults (rural-58%, urban-39%) are exposed to SHS at home (Global Adult Tobacco Survey (GATS) India 2010).

### Tuberculosis, smoking and second hand smoke

Smoking was independently associated with significantly increased risks of latent TB infection (LTBI). In certain populations, a greater risk of latent TB corresponded with increased smoking exposure is also observed (Horne et al. 2012). Exposure to SHS from tobacco in the household predisposes to the development of tuberculosis (TB) (Leong 2010). In addition, outcomes in TB patients gets worsen and risk of TB transmission increases if there is a continued exposure to SHS from tobacco. There is evidence showing significant association between SHS with drug resistant TB, severity of the disease, patient delay smear conversion and death during or after treatment. A systematic review and meta-analysis of observational studies reporting on relation of TB and tobacco revealed substantial evidence that tobacco smoking is positively associated with TB and SHS increases the risk of TB disease (Lin et al. 2007). Children are at high risk of acquiring TB infection that lives with adults who have had TB and are also smokers (Patra et al. 2012; Singh et al. 2005; Alcaide et al. 1996). Moreover, children who have had a recent TB infection are also five times more likely to develop active TB disease if exposed to SHS compared to children living in a smoke free environment (Alcaide et al. 1996).

### Smoking restrictions at home

It is crucial for better health of a family that their home should be free from tobacco smoke, as around 90% of the exposure to SHS takes place at home. This calls for restrictions for smokers to smoke inside the home which could be only achieved by rigorous work by identifying the smoker and convincing him/her not to smoke inside the home thus making a Smoke Free Home (SFH). Factors such as, younger age, being married, dislike for second hand smoke, and personal smoking behaviours such as smoking every day, on occasions, etc were found associated with having home and workplace smoking bans (Heck et al. 2010). In few cases, parents with younger children in home appear to have higher uptake of smoking bans than parents of older children or adolescents (Merom & Rissel 2001; Martinez-Donate et al. 2009). A qualitative study conducted in Scotland revealed that; the enablers to creating smoke free environment within the home include increasing awareness of the risks of SHS particularly in relation to children, desire to be seen as behaving in morally and socially acceptable ways, social norms about the unacceptability of smoking in the home among family and friends including pressure from children. Whereas, the barriers include limited understanding of and resistance to messages about the health risks of SHS, the need to smoke and smoker identity, the home perceived as a private space protected from public controls and sanctions, social norms among family and friends about the acceptability of smoking in the home (Philips et al. 2007). Awareness of the risks of SHS, despite ambivalence about health messages and the fluidity of smoking restrictions provides clear opportunities for public health initiatives to support people attain smoke-free homes.

#### Research problem and justification

Pakistan is low income country; and is known to have a 5^th^ highest TB burden and 9^th^ highest tobacco use among men in the world (World Health Organization 2012; Third WHO Report on the Global Tobacco Epidemic 2011). According to the World Health Survey, Pakistan (2002-2003), in adults 18 years and above prevalence of tobacco smoking was 19.1%, with males being 32.4% and females 5.7% respectively. In a survey conducted in one of the districts of Pakistan in 2008; 16.5% of the study population (33% men and 4.7% women) were found using tobacco on daily basis. The prevalence of exposure to SHS was found to be 56% (35% were exposed to SHS on daily basis and the remaining were exposed few times a week) (Alam et al. 2008). A survey of women on tobacco use and exposure to SHS during pregnancy showed that in Pakistan the SHS exposure in women was high. 91.6% homes allowed smoking indoors, 49.9% were frequently/always exposed to tobacco smoke indoors and 51.4% reported their young children being frequently/always exposed to tobacco smoke indoors (Bloch et al. 2008).

The government of Pakistan being the signatory of Framework Convention for Tobacco Control (FCTC) has already taken a number of important steps for effective tobacco control in the country including restriction on advertisement, health warning on cigarette packs, ban on sales to minors, mass media awareness, and legislations. According to current policy smoking is banned in health and educational facilities, offices and on public transportation. However, there are no clear guidelines and evidence is lacking on how to ensure a smoke free environment inside home for non smokers. There is currently no evidence on interventions, which could help to reduce exposure to SHS for non-smoker TB patients and help improve their TB outcomes by making their homes smoke free. This embarks on a need for innovative solutions within the context of TB care delivery which could provide evidence for creating SFH for TB patients which will be likely the main contribution of our proposed study. Similar interventions are being testing in educational settings (Siddiqi et al. 2010), but not done in the health care setting in risk groups such as TB patients. This is for the first time a pilot Randomized Control Trial (RCT) is going to be implemented in TB patients in making their home smoke free. Furthermore, such approaches have been highlighted in the declaration on Non Communicable Disease (NCDs) in United Nations summit held in September, 2011 (UN Sumit 2011) and also in World Health Organization 'MPOWER package’ (The MPOWER package 2008) and The Union 'Smoking cessation and smoke free environment for TB patients’ (Bissell et al. 2010).

#### Research questions

This pilot trial has been designed to answer the following research questions;
What behaviour change techniques are relevant and appropriate to be used in the development of 'Smoke Free Homes’ intervention?What is the feasibility and fidelity of implementing 'Smoke Free Homes’ intervention in TB patients?What is the proportion of non-smoker TB patients among all registered TB cases and what is the smoking behaviour of residents in their homes?What is the rate and reasons of refusal to participate in the research by the non-smokers with smoker in home?What are the recruitment and attrition rates for participants?What is the likely effect size in relation to the primary outcome measure i.e. reduction in the exposure to second-hand smoke validated by a urinary cotinine test after 2 months of TB treatment?What is the feasibility and acceptability of measuring the primary outcome?What are the barriers of change reported by the TB patient during follow-up?What is the feasibility of measuring TB treatment outcomes among trial participants?

#### General objectives

The purpose is to improve outcomes among those TB patients who are non-smokers themselves but are exposed to SHS and reduce the risk of TB transmission to other members of the household by encouraging families to make their homes smoke free.

#### Specific objectives

We aim to develop and evaluate a behavioural intervention 'Smoke Free Homes’ for TB patients. SFH for TB patients’ is a behavioural intervention that encourages TB patients to negotiate a smoke free environment within their homes. Our specific objectives are:
To develop a behaviour change intervention 'Smoke Free Homes’ aimed at encouraging families of newly registered non-smoking TB patients to implement smoking restrictions at home (Phase I).To conduct a pilot randomised controlled trial of 'Smoke Free Homes’ intervention within the context of routine TB control programme (Phase II).To determine the barriers and key drivers to the creation of SFH (Phase III).To develop and submit a proposal on a definitive trial based on the pilot trial findings (Phase IV).

## Methodology

### Design

This is a pilot individual randomised controlled trial of SFH that will inform the design of a future definitive trial. The definitive trial will assess the effectiveness and cost effectiveness of SFH intervention in reducing SHS exposure for non-smoking TB patients compared to routine care. We will first develop SFH intervention using taxonomy of behaviour change techniques (Michie & Abraham 2008) in order to help TB patients in negotiating smoking restriction at home. The selected Behaviour Change Taxonomy (BCTs) will guide the development of the content of the intervention tools likely to be in the form of a flip chart and a leaflet. This will be designed to inform and support TB patient to negotiate smoking restrictions in their homes.

### Objective 1

To develop a behaviour change intervention 'Smoke Free Homes’ aimed at encouraging families of non-smoking TB patients to implement smoking restrictions at home. (Phase I).

#### Key activities

The process of intervention development will run over 6 months period that will also include developing and finalising trial protocol and research tool. The development will take place in a phased manner following a logic model of the intervention (Figures 1 and 2). The logic model provides a pathway and focus to develop educational materials that improve knowledge, attitude, motivation, build confidence and negotiation skills, and increase intention to act with further reinforcement at the follow-up. It will be a two-pronged intervention where stage-1 will focus on the interaction between 'care provider and TB patient’ and stage-2 on the interaction between 'non-smoking TB patient and smoker(s) at home’.

**Figure 1 Fig1:**
[figure not shown]
**Intervention stage 1: health professional to non-smoking TB patient (who are exposed to SHS at home).**

**Figure 2 Fig2:**
[figure not shown]
**Intervention stage 2: TB patients to smokers in the home.**

The process of development will include organising a Development Core Group (DCP). The members will include representatives from the national TB control programme and tobacco control cell, media and communications expert, psychologist and the research team. The group will review the draft materials and approve these for piloting.

#### The intervention and its components

The SFH intervention will be based on behaviour change taxonomy (BCTs). The intervention will follow the following steps to bring about a change in the behaviour of the smoker living with the non-smoking TB patient: a) providing information to the non-smoking TB patient; b) helping him/her to formulate a strategy to change behaviour of the smoker and help sustaining that change; and c) finally giving a clear call to action for behaviour change.

#### Outputs

A complete set of refined SFH intervention materials including an illustrative flip chart to inform and encourage non-smoking TB patient to negotiate smoking restrictions at home.An illustrative leaflet for the TB patient that will help him/her to start a conversation on the topic of making the home smoke free.The intervention package will also include supplementary support which includes mobile phone standardized text messages or letter (where mobile phone is not available) on a weekly basis, to be sent to smoker at home in the arm 2 of the trial.

Figures 1 and 2 presents the logic model which presents the flow of events and the expected outcomes.

### Objective 2

To conduct a pilot randomised controlled trial of 'Smoke Free Homes’ intervention within the context of routine TB control programme (Phase II).

#### Hypothesis

We hypothesis that the SFH educational materials with or without supplementary support (mobile phone text message 'SMS’ or letter to smoker(s) at home on weekly basis) will be effective in relative or absolute reduction of exposure to tobacco smoke at home in non-smoking TB patients living with smoker(s). The option of supplementary support of SMS or letter seems more powerful as this may persuade the smoker at home in implementing smoking restriction in home.

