#### Study design and sample

The design of the trial is an individual randomised controlled trial (RCT). Figure 3 represents the overall flow of the events in the trial. To deliver 'Smoke Free Home’ intervention, the eligible non-smoking TB patients will be randomised and allocated to one of the two trial arms. **Arm 1** consists of “individual based care” i.e. SFH intervention materials, whereas **Arm 2** consists of “individual based care” plus “supplementary support” i.e. mobile phone text message or letter to smoker(s) at home with an assumption that it would persuade more the smoker to smoke outside the home. As it is a pilot RCT, we aim to recruit 150 newly registered pulmonary TB patients from two selected TB centres with 75 cases in each arm.

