#### Patient randomisation

The research team will draw simple randomisation tables where the unit of randomisation will be individuals. The 150 cases will be randomised in to two arms with 75 cases in each arm. The record of randomisation codes and allocation will be maintained by the principal investigator. Once randomised, a participant cannot be withdrawn from the trial. The RA will remain blinded to the fact regarding which arm has been allocated to the patient and will deliver the individual based care to all patients registered in the trial. Once a patient will be registered the information will be send by the RA to the principal investigator who will allocate the arm and inform the co-investigator. The SMS or letter to the arm 2 registered patients will be send by the researcher away from the TB centre. The trial register will be kept in researcher office under lock and key and only the principal investigator will have access to it.

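### Both arms receive the SFH materials, so no randomised comparison can test whether the materials reduce exposure or supply an effect size for SFH against routine care

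*Protocol article*

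**What the plan says.** The Hypothesis section (Objective 2) has two parts. The first begins "We hypothesis that the SFH educational materials with or without supplementary support" and predicts a relative or absolute fall in exposure at home. The second says "The option of supplementary support of SMS or letter seems more powerful", because it may persuade the smoker.

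Under Study design and sample, Arm 1 is the SFH materials, and Arm 2 is the same materials plus a text message or letter to the smoker. Under Patient randomisation, the research assistant "will deliver the individual based care to all patients registered in the trial". Data analysis (Objective 2) compares these two arms with each other, adjusted for health centre, and says that the sample was not powered for the effect size.

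Under Outcome assessments, urine cotinine is tested at registration and at 2 months, and the second test is meant to validate the intervention's effect.

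The sixth research question asks "What is the likely effect size in relation to the primary outcome measure", meaning reduced exposure confirmed by cotinine at 2 months. It names no comparator. The Design section says that the definitive trial will assess the "effectiveness and cost effectiveness of SFH intervention in reducing SHS exposure for non-smoking TB patients compared to routine care".

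**The concern.** The first part of the hypothesis is a claim about the materials themselves, including when they are used without support. Testing it by randomisation needs a group that does not receive them, and there is none. The definitive trial will ask the same question, SFH against routine care, and the pilot is meant to inform that trial.

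Two misreadings are open at the reporting stage. A fall in cotinine in both arms could be reported as evidence that SFH works with or without support, when it may have other causes. And a figure reported in answer to research question 6, whether the between-arm difference or a before-after change, could be carried into the planning of the definitive trial as if it were the effect of SFH against routine care.

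**Working it through.** **The plan's own figure.** The sample is 150, and 75 + 75 = 150 agrees. No alpha, power, effect size or rate is given, so there is nothing further to reproduce. The question is which effect the design identifies.

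**Set-up.** On whatever scale the outcome is defined, let
- b = change from 0 to 2 months that would occur under routine care,
- s = effect of the SFH materials against routine care,
- u = effect of adding SMS or letter to the materials.

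From the arm descriptions:
- expected change in Arm 1 = b + s
- expected change in Arm 2 = b + s + u
- randomised contrast, Arm 2 − Arm 1 = (b + s + u) − (b + s) = u

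Both b and s cancel. The first part of the hypothesis and the definitive trial are about s. The second part of the hypothesis is about u.

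**Numerical illustration.** All values of b, s and u are assumed, because the documents give none. They are improvements expressed as proportions, with u = 0.15.

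| b | s | Arm 1 change (b + s) | Arm 2 − Arm 1 |
|---|---|---|---|
| 0.30 | 0 | 0.30 | 0.15 |
| 0.20 | 0.10 | 0.30 | 0.15 |
| 0.30 | 0.10 | 0.40 | 0.15 |
| 0.10 | 0.30 | 0.40 | 0.15 |

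The between-arm difference is 0.15 in every row, although s runs from 0 to 0.30. Rows 1 and 2 give the same data in both arms with different values of s, and so do rows 3 and 4. Read as the effect of SFH, the Arm 1 change overstates s by b, here 0.10 to 0.30.

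**Why b need not be zero.**
- Diagnosis: participants are newly registered TB cases, and the household may change its smoking for that reason alone.
- Season: recruitment ran from November 2012 to the end of May 2013 (Trial status), so 2-month samples fall from about January to July 2013.
- Regression to the mean: entry requires living with a regular smoker who smokes in the house without restriction (Inclusion criteria), and households selected in an unrestricted state can drift back.

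The documents give no size for any of these.

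**Figure 3.** The flow chart is not shown, but Study design and sample, Patient randomisation and Data analysis agree on two arms that both receive SFH.

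**The case against.** The strongest reply is that this is a pilot. Most of its nine research questions concern intervention content, feasibility, recruitment, attrition, acceptability and barriers, and none of those needs a routine-care arm. That stands, and it limits the point to one part of the hypothesis and one research question.

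A second reply is that the protocol already says the sample is not powered for the effect size. That concerns precision. More patients would estimate u more closely and would still say nothing about s.

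The documents do not support some stronger readings that a reader might infer:
- *The hypothesis cannot be tested at all.* Its second part, that support is more powerful, is what the randomised contrast addresses. For the first part, the 0- and 2-month tests allow a weak, uncontrolled assessment.
- *Two equal arms would leave the pilot unable to tell success from failure.* The 0-to-2-month data separate no fall in either arm from a fall in both. Only the cause of a fall in both is ambiguous.
- *The protocol plans to size the definitive trial from the pilot's effect.* It does not say so. The key activities of Objective 4 name recruitment and attrition, with an open-ended et cetera. The link from research question 6 to the definitive trial is a reasonable reading, not a stated plan.
- *Fluctuation in spot urine would itself produce a fall.* Random fluctuation adds noise to a mean change. It gives a systematic fall only if entry selects on high cotinine, and no cotinine threshold is set.

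**Conclusion.** The point holds in this form: no randomised comparison in the pilot can test whether the SFH materials reduce exposure, and the pilot cannot supply a randomised effect size for SFH against routine care. Randomised information on that effect is zero at any sample size. This follows from the arm definitions alone and needs no numerical assumption. The 10 to 30 percentage point overstatement from a before-after reading is only an illustration and depends wholly on the assumed routine-care change.

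The pilot remains sound for feasibility, recruitment, attrition, outcome variability, the outcome level under SFH and, with limited precision, the increment from SMS or letter. It gives neither the 2-month outcome level under routine care nor the difference from it. No analysis plan could supply a randomised routine-care comparison among these participants.

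**What to change.** Recruitment is reported as complete, with data entry to follow the end of follow-up. Make the changes before analysis, dated and labelled as changes.

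1. **Hypothesis.** Make the hypothesis under test the one the design can address: adding SMS or letter to the SFH materials improves the 2-month cotinine-validated primary outcome, on whatever scale it is defined, over the SFH materials alone.
2. **Within-arm change.** State that changes from 0 to 2 months are descriptive and are not evidence that SFH works.
3. **Research question 6 and Phase IV.** State that the between-arm difference estimates only the SMS/letter increment. For the definitive trial, the pilot supplies recruitment, attrition, outcome variability and outcome level under SFH.
4. **Target effect of the definitive trial.** Justify the SFH-against-routine-care effect from another source. The Research problem and justification section says that no evidence yet exists on such interventions in non-smoking TB patients, so the source will probably be another population, and its relevance should be argued.

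The cost is wording and a narrower claim. No new arm, patients or measurements are needed.
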